### Randomization

Following the baseline survey, women who consented to participate were randomized into 1 of the following 4 experimental arms:

A control group (T0), in which a woman received a private counseling session on the full range of 13 contraceptive methods following a standard counseling process (n=100).An intervention group (T1), in which a woman was encouraged (but not compelled) to invite her husband to a joint counseling session. A woman (and her husband if she chose to invite him) then received a private counseling session on a full range of 13 contraceptive methods (n=200).An intervention group (T2), in which a woman received a private counseling session on 5 targeted contraceptive methods based on her baseline preferences for family planning (n=200).An intervention group (T3), in which a woman was encouraged to invite her husband to a joint counseling session. A woman (and her husband if she chose to invite him) was then counseled on 5 targeted contraceptive methods based on her baseline preferences for family planning (n=200).

Upon the completion of baseline data collection, women were randomized to 1 of the 3 intervention arms or the control arm, such that the intervention assignment was balanced along the following baseline characteristics: the use of family planning, most preferred method attributes, and age. As part of the balancing process, strata by each combination of characteristic values were created, and observations were assigned to their respective strata. Observations within each stratum were then individually randomized to each of the 4 groups by the principal investigator (PI) in a 2:2:2:1 allocation using computer-generated randomization using STATA, version 14 (StataCorp LLC). Following individual randomization, the Innovations for Poverty Action (IPA) Malawi intervention team implemented the intervention in the participants randomized into the intervention arms. Although the implementation team was not involved in the actual randomization process, counselors, who were responsible for administering the correct counseling and follow-up procedures to each respondent, were not blinded to respondent assignments to each of the intervention arms.

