### The Intervention

#### Intervention Protocols

All women who consented to participate in the study (T0-T3) were offered a free, private family planning counseling session, which included a risk assessment for contraceptive methods and detailed information on methods switching, side effects associated with each method, and the benefits of contraception and birth spacing. A precounseling survey was administered to each woman, where they were asked to confirm their personal information, including, but not limited to, pregnancy status, current contraceptive use, and preferences for fertility and contraception. During counseling sessions, counselors provided women with information on the range of modern and natural family planning methods based on their respective intervention assignments. Strategies on how to communicate family planning messages with partners and on how to increase partner awareness were conveyed during the sessions. The counseling session lasted no more than 1 hour and was administered in a private room by a counselor who was trained to provide family planning and reproductive health services. To facilitate an effective and open dialog with women during the counseling session, only female counselors were hired. Counselors were hired by IPA Malawi, held a nursing degree, and were trained on the range of counseling protocols over a week. We enlisted the support of the Malawi RHD and several international nongovernmental organizations who work on family planning, including Population Services International (PSI), BLM, the Family Planning Association of Malawi, and FHI360, to help us develop training materials and counseling resources. We also collaborated with the Malawi RHD, BLM, and PSI to assist with counselor training.

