#### Postcounseling Package of Services

Following the postcounseling survey, all women (and husbands who participated in the counseling session) were offered the following package of services for a 1-month period:

Transportation service: women (and applicable husbands) were offered a free transportation service from their homes to the Good Health Kauma Clinic for a period of 1 month. The transportation service was provided by a driver who was hired and trained by IPA Malawi. Respondents received the phone number of a female field manager and were instructed to let the field manager contact the driver to transport them to the Good Health Kauma Clinic during the clinic’s normal working hours, that is, from 8 AM to 5 PM from Monday to Saturday. The field manager maintained a daily schedule of respondents who requested the driver’s services, and the respondents were instructed to notify the field manager at least one day before they wish to go to the clinic to ensure that the driver would be able to transport them. The field manager also provided 1 day’s advanced notice to the Good Health Kauma Clinic to inform them of the number of clients who could be expected to attend the clinic on the following day. Each woman who visited the clinic was always accompanied by the female field manager; the presence of another woman in the vehicle acted to minimize potential stigma associated with a woman traveling alone in the company of a man and also provided comfort to the participant.Financial reimbursement for family planning services: finally, women and participating husbands were financially reimbursed for any out-of-pocket expenditures that they incurred for receiving family planning care at the Good Health Kauma Clinic for the 1-month service period. Costs that were eligible for reimbursement included the procurement costs of family planning medications and contraceptive methods, family planning consultation fees, lab test fees, treatment costs for any contraceptive-related side effects and contraindications, expenses associated with switching and discontinuation of methods, and exam fees. Each couple was allowed a maximum reimbursement amount of MWK 17,500 (US $25.00), which could be redeemed by the couple over multiple visits at the Good Health Kauma Clinic. The extent to which a given expenditure at the clinic met the criteria for being reimbursed was determined by the clinician. For every family planning service that was eligible for reimbursement, the cost of the service was deducted from her reimbursement allowance.

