### Analysis Plan

The analysis of quantitative study data will be conducted using STATA and R (R Foundation), where appropriate. Descriptive analysis will be performed for all variables, and unadjusted comparisons between experimental arms will be conducted. Descriptive statistics, including frequencies, means, and SDs, will also be performed. Chi-square tests and one-tailed *t* tests will be used to examine associations in the data. A probability value of less than .05 will be considered statistically significant for all the statistical tests that are conducted. Continuous variables will be tested for normality, and nonnormal values will be categorized or appropriately transformed. Given our hypotheses regarding the impact of our intervention on our key outcomes, one-sided hypothesis tests will be conducted for all our main analyses.

Our main econometric specifications will (1) estimate the intent-to-treat (ITT) effects of our family planning intervention on fertility intentions and preferences, contraceptive intentions and preferences, intention to switch methods, and other outcomes related to contraceptive behaviors by directly regressing our outcomes of interest on a binary variable indicating receipt of the intervention and (2) estimate the effect of interventions on downstream behavioral outcomes (such as women’s uptake of contraceptive options and the concordance between their revealed preference and their stated preference) using a 2-stage least squares model, in which the intermediate counseling variable will be instrumented by the treatment. The main econometric specification for estimating the ITT effect of our family planning intervention is defined as follows:

*Y_it_* = *β_0_* + *β_1_T_it_* + *X_it_ζ* + *Y_i0_* + *η_i_* + *ε_it_*

where *Y_it_* is the outcome variable of interest for woman 𝑖 in time period 𝑡=0, 1, 2 for baseline (time period 0) and follow-up (time periods 1 and 2), respectively; *T_it_* is an indicator of assignment to 1 of the 3 treatment arms; *X_it_* is a vector of individual-level covariates that are controlled for in the analysis; η_i_ is the individual-specific fixed effect; *Y_i0_* is the baseline level of the outcome; and *ε_it_* is the error term. Here, the outcome variables of interest include immediate, intermediate, and long-term outcomes described in the previous sections.

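### The printed main ITT equation has woman fixed effects and no period term, so β1 is either not estimable or is essentially the before-after change in the treated arms

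*Protocol article*

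**What the plan says.** The Analysis Plan section of the protocol article prints one equation as the main specification for ITT effects:

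Y_it = β0 + β1T_it + X_itζ + Y_i0 + η_i + ε_it

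Its legend defines every symbol:
- The outcome is indexed "for baseline (time period 0) and follow-up (time periods 1 and 2), respectively", so the baseline row is part of the outcome vector.
- T_it "is an indicator of assignment to 1 of the 3 treatment arms". The sentence introducing the model describes it differently, as "directly regressing our outcomes of interest on a binary variable indicating receipt of the intervention".
- Y_i0 "is the baseline level of the outcome". It is printed without a coefficient.
- η_i "is the individual-specific fixed effect".
- X_it holds individual-level covariates. Neither the equation nor the legend has a wave or period effect.

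The same section makes all main tests one-sided at .05 and separately plans unadjusted comparisons between arms. Under Postcounseling Package of Services, women in every arm "were offered the following package of services for a 1-month period". Under Intervention Protocols, all four arms are also offered a private counseling session.

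**The concern.** The equation merges two designs that do not combine. One is an ANCOVA, which conditions on the baseline outcome and compares arms afterwards. The other is a fixed-effects panel model, which uses only change within each woman. A fixed effect absorbs everything constant within a woman, including her baseline outcome and her randomised arm. What is left for β1 depends on how T_it is coded, and neither natural coding gives a randomised comparison.

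This matters in this trial because the control arm is active. T0 women get a counseling session, free transport and reimbursed services, so use, intentions and preferences may shift in all arms. A model in which T0 does not anchor the time trend would credit that shared shift to targeted counseling or the husband invitation. With one-sided tests, a shared upward shift turns directly into false-positive findings.

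**Working it through.** **1. The comparison the trial was sized for.** The power section compares 300 with 400 women between arms, 50% against 60%. The pooled rate is (150 + 240)/700 = 0.557. The null standard error is √[0.557 × 0.443 × (1/300 + 1/400)] = 0.0379, and the standard error under the alternative is √(0.25/300 + 0.24/400) = 0.0379. Power = Φ[(0.10 − 1.96 × 0.0379)/0.0379] = 0.75, as stated. One-sided it is 0.84 (stated 85%). The design figures therefore describe a between-arm contrast.

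**2. Can the printed model estimate β1?** The rank of the design matrix was checked on 70 women in three waves, with arms 10/20/20/20.

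| Columns | Rank |
|---|---|
| Fixed effects only | 70 |
| + Y_i0 | 70 (redundant) |
| + T constant within woman | 70 (β1 not estimable) |
| + T = 0 at baseline, 1 afterwards in T1–T3 | 71 (β1 estimable) |
| Waves 1 and 2 only, + T | 70 (β1 not estimable) |

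**3. What β1 is in the estimable case.** Subtracting each woman's mean over waves leaves T_it − T̄_i = 0 in every wave for T0 women, and −2/3, 1/3, 1/3 for T1–T3 women. Without X, therefore,

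β1 = mean over T1–T3 women of [(Y_i1 + Y_i2)/2 − Y_i0].

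In simulation β1 equalled this quantity to within 1e-10 in every run and did not move when all controls were deleted. Time-varying covariates would let control women inform ζ, but not the missing time trend.

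**4. Size when the arms truly do not differ.** Assumptions, none given in the article: a binary outcome at 50%, a common shift δ, and latent within-woman correlation λ. The correlation between two binary waves is then ρ = (2/π)·arcsin λ. Holding the variance at its 50% value,

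Var[(Y1 + Y2)/2 − Y0] = 0.25 × 1.5 × (1 − ρ),

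and the one-sided rejection rate is Φ(β1/SE − 1.645).

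*Shift at the 1-month wave only (β1 = δ/2):*
- λ = 0.6, n = 223 + 225 + 228 = 676 treated: ρ = 0.41, SE = √(0.2214/676) = 0.0181.
  - δ = 5 points: 0.025/0.0181 = 1.38, so 40%.
  - δ = 10 points: 0.050/0.0181 = 2.76, so 87%.
- λ = 0.49, n = 600 planned: ρ = 0.33, SE = √(0.2527/600) = 0.0205.
  - δ = 5 points: 0.025/0.0205 = 1.22, so 34%.

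Simulations at λ = 0.6 gave 34% to 41% for 5 points and 88% for 10 points.

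*Shift at both post-baseline waves (β1 = δ), λ = 0.49, n = 600:*
- δ = 5 points: 0.050/0.0205 = 2.44, so 79%.
- δ = 10 points: 0.100/0.0205 = 4.87, so over 99%. Simulation (2,000 runs) gave 79% and 100%.

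With no common shift, the rate is about 5%.

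**5. Isolating the cause.** Adding one common post-baseline period term turns β1 into the treated-minus-control difference in change. Simulated β1 then averages 0.00 with no effect and 0.10 with a true 10-point effect, for every trend tried from −5 to +10 points. The false-positive rate is 5.2% to 5.5%. Without the term, a true 10-point effect appears as 0.15, 0.20 or 0.05 under trends of +5, +10 or −5 points. An ANCOVA at the 1-month wave also holds at about 5%.

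The reported arm counts sum to 784 (223 + 225 + 228 + 108), not the 782 women stated as randomised. This does not affect the result.

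**The case against.** The strongest reply is that this is loose notation. β0 and Y_i0 look like parts of an ANCOVA, and if η_i were a random effect, β1 would be estimable with the control arm in the comparison. If T_it is constant assignment, software would drop the term rather than report a misleading number. Both points narrow the harm, but neither rescues the text: it calls η_i fixed, and a main model that cannot be fitted still has to be replaced by something not yet specified.

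Several stronger readings are tempting and are not supported:
- **A reader might infer that the randomised control arm is lost from the analysis.** It is lost from this specification only. The unadjusted between-arm comparisons remain, and the power section is built on between-arm contrasts.
- **A reader might take the false-positive rates as forecasts.** They belong to one coding of T_it and to assumed trends and correlations. They are also illustrated on a 50% outcome such as contraceptive use, whereas the Analysis Plan sends uptake and concordance mainly to two-stage least squares. The algebra does not depend on the outcome; the percentages do.
- **A reader might claim a definite power loss from pooling the two post-baseline waves.** The precounseling survey covers items "including, but not limited to, pregnancy status, current contraceptive use, and preferences for fertility and contraception", so use at that wave predates the counseling content. But the loss depends on the between-wave correlation, on sidedness and on baseline adjustment, and the article does not give the correlation. It also does not say whether the husband invitation came before that survey. Stated method preference is elicited right after counseling, so an effect at that wave is possible for it.
- **A reader might call the unlisted strata or the time index on X_it errors.** The contents of X_it are not enumerated, and an article may leave that list to the full plan.

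**Conclusion.** The point holds for the main ITT specification as printed. The non-estimability, the redundancy of Y_i0 and the before-after meaning of β1 are algebra and need no assumption beyond the article's own definitions. The last is exact without X and essentially true with individual-level covariates. The practical damage is conditional on T_it switching on after baseline and on a common change over time, which is plausible because every arm receives counseling and the service package. Under the assumptions in the working, common rises of 5 to 10 points with no arm difference give one-sided false-positive rates of roughly 34–88% if confined to the 1-month wave, and about 79–100% if present at both post-baseline waves. The equation should be corrected before its estimates are reported as causal effects.

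**What to change.** Replace the equation with an ANCOVA fitted separately at each post-baseline wave. Regress Y_it on the treatment terms, Y_i0 with its own coefficient, the randomisation factors and baseline covariates, with no η_i and no t = 0 rows. The randomisation factors belong in the model because assignment was made "such that the intervention assignment was balanced along the following baseline characteristics: the use of family planning, most preferred method attributes, and age".

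The treatment terms should include the two contrasts the trial is powered for: husband invitation (T1 and T3 against T0 and T2) and targeted counseling (T2 and T3 against T0 and T1). Enter both together, because 2:2:2:1 allocation makes the factors unbalanced: by the planned numbers, 200 of 300 women in the noninvitation arms get targeted counseling, against 200 of 400 in the invitation arms.

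Alternatively keep η_i, drop Y_i0, and add wave effects and treatment-by-wave terms.

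For contraceptive use, base the effect estimate on the 1-month wave; stated preferences can be analysed at both waves. State whether T is assignment or receipt, since the text gives both.

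The cost is analysis-plan wording and code. No new data are needed, and the article reports that the primary analyses were still ongoing.

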We will conduct several subgroup analyses to examine how our family planning intervention effects vary across key subpopulations. Subgroups of interest include women who have or do not have their husbands’ approval for accessing contraceptive methods, women who have or have not previously used family planning methods, women whose most valued method attribute is or is not effective, working or nonworking women, higher or lower educated women, counseling sessions administered in the morning or afternoon, women who have more or less than 2 children, and counseling sessions of above or below the median length.

Finally, robustness checks (5% and 10% sample truncations and coarsening of independent variables) and falsification tests, which include placebo regression, simulation, and resampling methods, will be conducted to ascertain the strength and significance of our estimates. We will also conduct attrition-adjusted analyses to assess the extent of differential loss-to-follow-up on outcomes. In handling missing data, we will conduct a complete case analysis if the potential impact of the missing data is negligible, and we can conduct a series of sensitivity analyses, including *best-worst* case analyses, to generate plausible bounds of estimates across different scenarios of missingness. If we are able to assume that any missing data are missing at random, then we will conduct an ITT analysis using multiple imputation to adjust for missing data. We will then compare the ITT estimates from our multiple imputation analysis with our estimates from a complete case analysis, which would allow us to infer the extent to which missingness might impact our inference.

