### Sample Size and Power Calculations

#### Target Sample and Key Outcomes

The sample size of this study was powered to primarily identify the independent effects of tailored family counseling and male involvement on women’s contraceptive uptake and switching of methods. On the basis of the preliminary power calculations for the primary outcomes of interest, our target baseline sample consists of 700 eligible women who consent to participate in the study. Among these 700 women, 100 women were assigned to the control arm T0, and 200 women were assigned to each of the 3 intervention arms, namely, T1, T2, and T3.

Previous studies have found that one-fifth of women of reproductive age were either pregnant or had given birth to a child in the past 6 months [40]. To meet our target sample size of 700 women who would be eligible to participate in our study, we need to recruit a total of 940 women if we conservatively assumed a combined ineligibility or refusal rate of 25%.

We have powered our study to detect effects on the following outcomes: (1) contraceptive uptake and (2) intention to switch from the current contraceptive method.

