### Study Limitations

Our study has several limitations. Although the study is powered to independently test the effects of 2 user-centered counseling procedures on women’s stated and realized preferences, the sample size of this study may be too small to allow for the examination of interaction effects across treatment arms. As an exploratory exercise, we will examine these effects and present them as supplementary findings. Moreover, although our study can infer the manner in which women realize their preferences in response to counseling, it is not as straightforward to be able to disentangle a woman’s true individual preferences for family planning from her stated preferences in the presence of her partner, who is likely to influence her eventually realized choice (or lack of choice) of method. To this end, additional research is warranted to better understand how women’s true preferences are expressed and can be documented, even in cases where their partner is present. Similarly, it would be equally necessary to further explore the trade-off that women face between (1) making independent decisions to reflect their individual preferences and (2) incorporating their husband’s/family’s preferences to make jointly/socially better-off, but not necessarily individually better-off, decisions.

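### Eight subgroup factors fall under a blanket p<.05 rule with no exploratory label; if several outcomes are tested, a false subgroup result is likely

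*Protocol article*

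**What the plan says.** The Analysis Plan section commits to subgroup work: "We will conduct several subgroup analyses to examine how our family planning intervention effects vary across key subpopulations". The factors are the husband's approval, previous family planning use, whether effectiveness is the most valued attribute, work, education, morning or afternoon session, number of children, and "counseling sessions of above or below the median length". The text names no outcomes, no interaction test and no limit on which intervention contrasts are examined.

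Earlier in the same section the decision rule is set: "A probability value of less than .05 will be considered statistically significant for all the statistical tests that are conducted". On direction, it says "one-sided hypothesis tests will be conducted for all our main analyses", and it also specifies one-tailed t tests for associations.

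Target Sample and Key Outcomes says the trial is powered for the "independent effects of tailored family counseling and male involvement", on two outcomes: contraceptive uptake and intention to switch. Primary Outcomes lists seven domains.

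Study Limitations says the sample may be too small for interactions between treatment arms, and then: "As an exploratory exercise, we will examine these effects and present them as supplementary findings". That label covers the between-arm interactions. Nothing similar is said of the subgroups.

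**The concern.** Read together, these statements let any subgroup result with p<.05 be declared statistically significant. This is a stated rule, not silence that an analysis plan would fill: a plan that adjusted or exempted the subgroup tests would depart from the published threshold. The authors downgraded one underpowered analysis and not the other.

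Two errors could follow. If neither intervention works, some subgroup may still appear to benefit by chance. If an intervention works equally well for everyone, reduced power within each subgroup can make one level significant and the other not, which is easily misread as a differential effect. The article expects partners to use its findings to tailor services, and subgroup claims lend themselves to that use.

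**Working it through.** **Inputs from the article.** Eight two-level factors and α = .05 (Analysis Plan); two interventions and two powered outcomes (Target Sample and Key Outcomes); 300 v 400 women per factor comparison, with 50% v 60% for prevalence and 20% v 30% for switching (power subsections); 2:2:2:1 allocation (Randomization); 731 completed follow-ups (Follow-Up Surveys).

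**Assumptions not in the article.** Both interventions and two outcomes are tested for every factor; splits are 50/50; factors and outcomes are independent or correlated as stated below.

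**1. Stated power reproduces.** Power = Φ{[d − z·SE(pooled)] / SE(unpooled)}.
- 50% v 60%, 300 v 400: pooled p = 390/700 = .557, SE(pooled) = .0379, SE(unpooled) = .0379.
- Two-sided: (.1 − 1.96 × .0379)/.0379 ≈ 0.68, power .751 (stated .75). One-sided: .840 (stated .85, within rounding of a method difference).
- 20% v 30%: .856 two-sided (stated .86) and .917 one-sided (stated .92).

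**2. Number of tests under the assumptions.** 8 factors × 2 interventions × 2 outcomes = 32 heterogeneity questions. Two levels each gives 64 within-subgroup tests.

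**3. Chance of at least one false positive, independent tests.** 1 − .95^k: k = 8 gives 33.7%, k = 16 gives 56.0%, k = 32 gives 80.6%. For 64 within-subgroup tests independence is not credible, because each woman is reused in all eight factors. The expected number of false positives (64 × .05 = 3.2) still holds.

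**4. Allowing for correlation.** Simulation under no effect: 731 women in arms of 104/209/209/209, eight balanced factors, binary outcomes at 50% and 20%, both interventions estimated jointly, 1,200 trials per scenario, latent correlation 0-0.9 between outcomes and 0 or 0.5 between factors.

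| Tests assumed | At least one false positive |
|---|---|
| 64 within-subgroup, one-sided .05 | 66-77% |
| 32 interaction tests, two-sided .05 | 72-82% |
| Both interventions, one outcome (within-subgroup or interaction) | 47-57% |
| One intervention, one outcome, within-subgroup | 27-32% |

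About 3 of the 64 tests are falsely positive per trial. If the outcomes themselves, rather than their latent scales, are correlated at 0.9 and the factors at 0.5, the within-subgroup figure falls to roughly 54-57%.

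**5. A uniform true effect.** Halving the sample to 150 v 200 for 50% v 60%: SE(pooled) = .0537, SE(unpooled) = .0535.
- One-sided: (.1 − 1.645 × .0537)/.0535 ≈ 0.22, power .587. Two-sided: ≈ −0.10, power .462.
- Chance that exactly one of two levels is significant = 2 × power × (1 − power): 2 × .587 × .413 = 48% one-sided; 2 × .462 × .538 = 50% two-sided.
- 20% v 30%, one-sided power .69: 2 × .69 × .31 = 43%.

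**6. Two factors are not baseline factors.** Counseling comes after randomization, so session length and time of session are observed after assignment. Targeted counseling covers 5 methods rather than 13, so assignment may itself change session length. Women in short sessions would then not be comparable between arms.

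**The case against.** The strongest reply is that the article does not lay down the test grid. It names no outcomes for the subgroups, and its aim of seeing how effects vary fits an interaction test at least as well as separate tests within each level. The .05 sentence sits in a paragraph about descriptive and association tests and may only define nominal significance. The choice of test and any multiplicity handling could belong in a fuller plan. Subgroups appear in neither the hypotheses nor the power section, so their secondary role is visible, and no text proposes recommendations for particular subgroups.

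Much of this stands. A reader might infer that 32 or 64 tests are planned, all one-sided, and that a false subgroup finding is therefore more likely than not. The documents do not support that as fact: the count is an assumption, the one-sided rule is stated for the main analyses and for t tests, and the claim fails for one intervention on one outcome and is borderline for both interventions on one outcome.

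What does not stand is the appeal to a fuller plan. The .05 sentence covers all tests conducted, and the exploratory label was given to a different analysis. Using interaction tests does not help either, since at an unadjusted .05 they give a similar error rate. The placebo, simulation and resampling checks listed in the same section are not a multiplicity adjustment.

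**Conclusion.** The concern holds in a limited form. The article lists eight subgroup factors, applies an unadjusted .05 rule to every test and does not call the subgroups exploratory. Assuming two interventions, the two powered outcomes and balanced splits, the chance of at least one false subgroup result when nothing works is about 65-80%, whether by one-sided within-subgroup tests or two-sided interaction tests. It is lower if outcomes are almost interchangeable, about 50% for both interventions on one outcome and about 30% for one intervention on one outcome. With seven primary domains listed, two outcomes is not an extreme assumption. Under a uniform 10-point effect, close to half of subgroup pairs would be discordant by chance.

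The result does not depend on one-sided subgroup testing, which the article does not specify. The main comparisons are unaffected; the risk lies in how subgroup results are declared and used.

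**What to change.** Add to the Analysis Plan:
- Subgroup analyses are exploratory and exempt from the p<.05 rule.
- For each baseline factor, variation is judged only by the treatment-by-subgroup interaction, two-sided, as a difference in effects with its confidence interval, separately for husband invitation and targeted counseling.
- Within-subgroup estimates are given with confidence intervals and no significance claims.
- If any heterogeneity is to be called significant, it must be by a multiplicity-adjusted interaction test, with the set of factors, interventions and outcomes named beforehand. For scale, Bonferroni over 32 tests would be .05/32 = .0016 each.
- Session length and time of session are reported apart from the baseline subgroups, as post-randomization descriptive splits.

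The cost is a few sentences and no new data. The downside is that fewer subgroup results can be called significant. The article reports primary analyses as still ongoing, so the wording should be settled before subgroup results are interpreted.
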